## Abstract

**Background:**

The early life period represents the first step in establishing a beneficial microbial ecosystem, which in turn affects both short and longer-term health. Changes during pregnancy influence the neonatal microbiome; through transmission of maternal microbes during childbirth, and beyond, through nutritional programming. However, in-depth exploration of longitudinal maternal-infant cohorts, with sampling of multiple body sites, complemented by clinical and nutritional metadata, and use of cutting-edge experimental systems are limited.

The PEARL study will increase our knowledge of; how microbes (including viruses/phages, bacteria, fungi and archaea) change in composition and functional capacity during pregnancy; transmission pathways from mother to infant; the impact of various factors on microbial communities across pregnancy and early life (e.g. diet), and how these microbes interact with other microbes and modulate host processes, including links to disease onset.

**Methods:**

PEARL is a longitudinal observational prospective study of 250 pregnant women and their newborns, with stool and blood samples, questionnaires and routine clinical data collected during pregnancy, labour, birth and up to 24 months post birth.

Metagenomic sequencing of samples will be used to define microbiome profiles, and allow for genus, species and strain-level taxonomic identification and corresponding functional analysis. A subset of samples will be analysed for host (immune/metabolite) molecules to identify factors that alter the host gut environment. Culturing will be used to identify new strains of health-promoting bacteria, and potential pathogens. Various *in vitro* and *in vivo* experiments will probe underlying mechanisms governing microbe-microbe and microbe-host interactions.

**Discussion:**

Longitudinal studies, like PEARL, are critical if we are to define biomarkers, determine mechanisms underlying microbiome profiles in health and disease, and develop new diet- and microbe-based therapies to be tested in future studies and clinical trials.

**Trial registration:**

This study is registered in the ClinicalTrials.gov Database with ID: NCT03916874.

**Supplementary Information:**

The online version contains supplementary material available at 10.1186/s12887-021-02835-5.

## Background

The human gut microbiota comprises a complex microbial ecosystem (including viruses/phages, bacteria, fungi and archaea) which benefit their host through acquisition of additional nutrients and energy from dietary components, optimised development of the immune system, and resistance against pathogens [1, 2]. As the neonatal gut is essentially sterile, these beneficial microbes and their associated functions, must be acquired during and after birth; this is achieved through initial colonisation by pioneer bacteria, successive diversification, and changes in microbial population densities over time, until a climax or ‘stable’ microbiome is established during infancy and early childhood (Fig. 1) [3, 4].

**Fig. 1 Fig1:**
[figure not shown]
Overview of development of the microbiome during early life and the factors that influence this

The initial colonisation and establishment of the gut microbiome during early life influences physiological and immune development [4]. Critically, disturbances within this pioneering microbial community (both in mother and infant) have the potential to increase the risk of developing diseases such as autoimmune conditions, allergic-type disorders, infections and chronic intestinal diseases [4–6]. Factors such as antibiotic usage, diet (i.e. breast versus formula milk) and birth mode (i.e. Caesarean section versus vaginal) can affect the gut microbiota during this time (Fig. 1) [7–9].

Transmission of microbial species from the maternal microbiome to the infant occurs at birth, with subsequent waves of colonisation occurring as the infant ages [10–12]. There is also an increasing awareness of the importance of maternal health during pregnancy for infant development and health, both before and after birth [13]. Importantly, these life stage events appear to be governed by particular interactions (immune and dietary) that ‘select’ beneficial microbes such as *Bifidobacterium* [4, 14, 15]. Species in this genus are prevalent in the gastrointestinal tract of mothers in the later stages of pregnancy and can represent up to 80 % of the total microbiome in healthy infants [14, 16, 17]. These pioneering microbial species and strains contribute to ecosystem structuring, which is heavily influenced by their ability to metabolise complex sugars presents in breast milk – human milk oligosaccharides [17].

Although several studies have looked at these key factors at these critical timepoints, there are still many unknowns with respect to this key developmental window including; how the microbiome changes in response to different phases of pregnancy across different body sites; whether microbes from mothers are directly passed to infants during birth, and how birth mode affects this (i.e. vaginal birth vs. C-section); how factors like diet and antibiotics influence the maternal microbiome, and what impact this has on developing infant microbial communities; how different feeding regiments (e.g. breast vs. formula milk) influence specific microbial populations in the infant (e.g. *Bifidobacterium*); how these microbes influence immune and metabolic health.; and if in-depth mechanistic studies using *in vitro* and *in vivo* models can determine how specific microbes and communities contribute to healthy development and prevent disease incidence.

Longitudinal pregnancy and infant studies like PEARL, will provide an invaluable resource to study the importance of the early life microbiome. Gathering these data is critical for identification and development of new therapies and health- associated practices to improve health, both in the short- term and across the life course.

### Objectives

The primary objective of the PEARL study is to describe the determinants, function and composition of maternal and neonatal microbiomes throughout pregnancy and early childhood in a cohort of mothers and babies without serious health conditions.

Other objectives of this study are;

to link or correlate microbiome profiles to routinely collected clinical information in mothers and infants (e.g. antibiotic usage, birth mode) and dietary information via questionnaires (e.g. breast vs. formula milk), and to host metabolites and immune markers (e.g. cytokines) measured in samples collected;to use microbiome samples in preclinical models to describe the role that the early- life microbiome plays in immune and metabolic development and resistance to diseases;to use analysis and microbiome samples (using *in vitro* and preclinical models) to characterise the cause, effect and consequences of disturbances in the early-life microbiome due to external factors (e.g. antibiotics, birthing method, diet) on subsequent health outcomes;to define and characterise early-life associated microbiome species (e.g. *Bifidobacterium* species and *Enterococcus* species) from samples for their probiotic/pathogenic traits (using *in vitro* and preclinical models).

An additional key output, which will be available to the wider research community, is a comprehensive collection of microbiome samples and associated clinical and diet/lifestyle information that will be accessible via requests to [name] and the Norwich Research Park (NRP) Biorepository, with all microbiome sequence data publicly available after deposition in public repositories.

## Methods

PEARL is a longitudinal study of 250 pregnant women and their new born(s). Biological samples and data will be collected in pregnancy, labour, birth and up to 24 months post birth. In the event of multiple live births, each infant will be included. Figure 2 provides an overview of the overall design of the study and shows which samples and data are collected at each timepoint. There are up to 12 collection timepoints, as well as 4 optional blood sample donations which will be collected at routine maternity care appointments. The study is divided into 3 collection phases: pregnancy, birth to 4 months, and 4 months to 24 months post birth.

**Fig. 2 Fig2:**
[figure not shown]
PEARL study overview

Pregnant women can be recruited to PEARL at any time up to 22 weeks gestation. During phase 1 participants will be asked to collect samples and complete questionnaires during each of the three trimesters of pregnancy if they are involved in the study at that point. Participants are also able to donate blood samples at weeks 12, 16, 20, 28.

During phase 2, participants will collect samples at three timepoints from themselves and their infant(s); birth, at 1 week post birth, and at 3 weeks post birth.

Phase 3 collections will be every 4 months (4, 8, 12, 16, 20 and 24 months). With the exception of month 4, further collections of samples will be from the infant only.

At each collection time point, there is a window of 7 days within which the participant can collect their samples. This is to provide as much flexibility for participants as possible. Participants will receive a reminder message via text message or email when their samples are due to be taken, and again towards the end of the timepoint window.

Most samples will be collected at home using packs provided to the participants. The participants will be provided with a small freezer where they will store their samples until collected by a member of the research team. This freezer will be dedicated to holding study samples to minimize any cross-contamination risks to the participant. Collections from the participants’ homes will occur at 4 points throughout the study after phase 1, after phase two and at month 12 and month 24 during phase 3.

At birth, or any time the participant or her infant is an inpatient at the Norfolk and Norwich University Hospitals NHS Foundation Trust (NNUH), participants can collect their samples at the NNUH and give them to their midwife/obstetrician who will put these in the PEARL study freezer located at the hospital.

The sample collection protocol has been designed using significant optimisation information from our previous study, BAMBI [18], with additional information gathered from other longitudinal cohort studies including the Flemish Gut Project [19], and we are confident that our current protocol will allow participants to easily collect and store samples at -20◦C until collection.

After collection from participants’ homes, all samples will be appropriately aliquoted and will be stored in QIB at -80 °C prior to analysis. Additional aliquots may also be stored at the NRP Biorepository at -80 °C for future research if the participant has provided this additional consent.

Participants will complete 3 questionnaires during the study (timepoints detailed in Fig. 2) including questions on health, lifestyle, and diet. The questionnaires include:

Centre for Disease Control and Prevention (CDCP) questionnaires for pregnancy, breastfeeding and infant feeding practices [20]. Modified, with permission, for the purposes of this study (supplementary files 1, 2, 3, 4, 5, 6 and 7).A health questionnaire to provide information on lifestyle, diet and medication/medical history, developed for the study (supplementary files 8 and 9).A dietary perceptions and preferences questionnaire, developed for the study (supplementary files 10, 11 and 12).

The research team will also collect; clinical information from GP and hospital records that relate to any change in the participants or her infants’ medical history during the course of the study; routine data collected by health visitors (developmental Ages & Stages data) which includes information on fine and gross motor skills and problem solving; and routine pregnancy scans and tests.

### COVID19 mitigation strategies

In response to the COVID-19 pandemic, it is important to implement a risk mitigation strategy to protect the health and safety of both participants and researchers. Participants will be advised that they should not collect samples if they or anyone in their household has COVID19 symptoms, are self-isolating, are awaiting test results, or have in the last 70 days tested positive for COVID19. The research team will send collection packs and arrange the collection of participants’ samples following Standard Operating Procedures (SOPs)/ COVID-19 risk-assessments.

### Participant selection

#### Sample size

PEARL will recruit 250 pregnant women. Our primary aim is to detect associations between aspects of neonatal and maternal microbiomes, and their associations with external factors. As an indicative power calculation, if a potential risk factor has a prevalence of 25 % (recent data suggests that 25 % of mothers who deliver at our recruitment hospital [Norfolk and Norwich University Hospitals NHS Foundation Trust – NNUH] do not initiate breast feeding; the UK Caesarean section rate is also currently around 25 %). Then with 200 observations we would have power of 80 % to detect a difference of 0.46 standard deviations in any given outcome measure between those with and without the feature at a *p*-value of 0.05. This is commonly understood to correspond to a ‘moderate’ size of effect between an exposure and an outcome.

For continuous outcomes or correlations between 250 mother and baby pairs, we would be able to detect correlations of *r* = 0.2 with 80 % at *p* < 0.05. This corresponds to a continuous feature accounting for r2 = 4 % of the population variation in any given characteristic of the microbiome.

For secondary analyses, if the *p*-value threshold for statistical significance is corrected to *p* < 0.005 to account for multiplicity then the corresponding smallest detectable differences are 0.6 standard deviations between groups defined by a binary factor (e.g. mode of delivery or breastfeeding) or correlation of 0.25 between continuous variables.

Previously, Azad et al. [21] explore effects of maternal antibiotic use, mode of delivery and breastfeeding on diversity and major taxon abundance among a cohort of 198 Canadian neonates at 3 and 12 months of age. Differences in the three most abundant taxa between elective Caesarean section (*n* = 19) and vaginal births (*n* = 96) were detected at 3 months with *p*-values of < 0.001 and < 0.01, corresponding to effect sizes of > 0.63 and > 0.49 standard deviations.

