Early in the pandemic, the PEARL study had to temporarily pause research activities while risk assessments could be urgently revised and adaptions to processes could be established to ensure safety of both participants and staff. We developed a remote process to recruit participants and introduced a reduced collection schedule from participants’ homes to reduce any face to face contact involved in taking part in the study. All sample collections adhere to local and national guidelines on COVID-19 restrictions set out by the government.

During a second wave of the pandemic and increased pressure on local NHS trusts, we had to temporarily pause all recruitment activity to release any NHS resource that we were using for recruitment activities.

We have seen an increased withdrawal rate to the study at times when local restrictions for COVID-19 have been implemented which could be attributed to the increased stress brought on by these ‘locked down’ environments, such as increased workload of working families to home school children. Therefore, not wishing to continue in the research environment.

We have made several amendments to the study to increase safety of participants and research staff during the pandemic, with the hope that these actions will mean the PEARL study will not be affected in the long term.

It is likely COVID-19 will have implications on future studies and risk assessments should be made prior to set up.

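### The correlations said to be detectable with 250 mother-baby pairs do not follow from that number at 80% power: N, r and power in one sample-size statement are mutually inconsistent

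*Protocol article*

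**What the plan says.** All the figures are in the Sample size section of the protocol article.

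- Recruitment target: "PEARL will recruit 250 pregnant women".
- Binary exposure with 25% prevalence, threshold 0.05: "Then with 200 observations we would have power of 80 % to detect a difference of 0.46 standard deviations".
- Correlations: "For continuous outcomes or correlations between 250 mother and baby pairs, we would be able to detect correlations of". The value named there is r = 0.2, and its power and threshold are given as "with 80 % at *p* < 0.05". The word power is not repeated, but the sense is clear from the preceding paragraph.
- Gloss on the correlation: "This corresponds to a continuous feature accounting for r2 = 4 % of the population variation".
- Secondary analyses at p < 0.005: 0.6 standard deviations for a binary factor, "or correlation of 0.25 between continuous variables". N and power are not restated; these are presented as the values corresponding to the preceding ones.

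The section gives no attrition rate, does not say whether tests are two-sided, and does not explain why one calculation uses 200 and the other 250.

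**The concern.** For a correlation, fixing N, the significance level and the power fixes the detectable r. The set 250, 0.05, 80% and r = 0.2 can therefore be checked directly, and it fails.

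The section puts associations between maternal and neonatal microbiomes within the primary aim, and these are the only power figures offered for mother-baby correlations. As printed, a reader cannot tell what the study can detect or on how many analysed pairs. If 250 is meant, the stated r (or the stated power) is wrong. If another number was used, the N is wrong. It also stays unclear whether the figures leave any room for losses from the 250 women recruited.

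**Working it through.** **Inputs.** From the Sample size section: N = 250 pairs; r = 0.2 at 0.05; r = 0.25 at 0.005; power 80%; for the binary factor, N = 200 split 25:75, with 0.46 and 0.6 standard deviations (SD). Two-sided testing is my assumption; it reproduces the binary figures.

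**Normal quantiles.** 1.9600 (two-sided 0.05), 2.8070 (two-sided 0.005), 0.8416 (80% power), 1.2816 (90% power). The sums for 80% power are 2.8016 and 3.6487.

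**1. Binary-factor figures.** Detectable d = (z_alpha + z_power) × sqrt(1/n1 + 1/n2). With n1 = 50 and n2 = 150 the root is 0.1633.
- At 0.05: 2.8016 × 0.1633 = 0.457 (noncentral t: 0.460). Printed 0.46; reproduced.
- At 0.005: 3.6487 × 0.1633 = 0.596 (noncentral t: 0.602). Printed 0.6; reproduced.
- With N = 250 they would be 0.41 and 0.53 SD.

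**2. Pairs needed for the printed correlations at 80% power.** N = ((z_alpha + z_power)/atanh(r))² + 3.
- r = 0.2, 0.05: (2.8016/0.2027)² + 3 = 193.97, so 194.
- r = 0.25, 0.005: (3.6487/0.2554)² + 3 = 207.07, so 208.

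Neither is 250.

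**3. Detectable r.** r = tanh((z_alpha + z_power)/sqrt(N − 3)).

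| N | Power | r at 0.05 | r at 0.005 |
|---|---|---|---|
| 250 | 80% | 0.176 (r² = 3.1%) | 0.228 (r² = 5.2%) |
| 200 | 80% | 0.197 | 0.254 |
| 250 | 90% | 0.203 | 0.254 |
| Printed | 80% | 0.2 (r² = 4%) | 0.25 |

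**4. Power at the printed correlations.** Power = Phi(atanh(r) × sqrt(N − 3) − z_alpha).
- N = 250: r = 0.2 gives Phi(3.186 − 1.960) = 89.0%; r = 0.25 at 0.005 gives Phi(4.014 − 2.807) = 88.6%.
- N = 200: 81.2% and 78.2%.

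**5. Other methods for N = 250, r = 0.2, 0.05.** Bias-corrected Fisher z gives 89.1% and the noncentral F for simple regression 89.5%. One-sided testing moves further away, to 93.8%. No standard variant returns 80%.

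**The case against.** The discrepancy is small and errs on the safe side. The calculation is offered as indicative, and the sentence says r = 0.2 can be detected without calling it the smallest detectable value. With 250 pairs that claim is met with power to spare, and 0.176 would even print as 0.2 to one decimal. The direction and the modest size stand. The rounding explanation does not: the text goes on to state 4% of variance where 250 pairs give 3.1%, and the second correlation is printed to two decimals as 0.25 where 250 pairs give 0.23. That second figure is tied to 250 only by being called the corresponding value, so the main weight rests on the first.

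Three stronger readings are tempting, and the document does not support them.

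- *That the figures were certainly computed for 200 pairs.* The binary paragraph ("Then with 200 observations we would have power of" 80%) makes this more likely, but 250 pairs at 90% power reproduces both correlations equally well, so a misprinted percentage is also possible.
- *That the plan builds in 20% loss.* 200 is 80% of 250, but no loss rate is stated and nothing links the two numbers. The Discussion reports that "We have seen an increased withdrawal rate to the study at times when local restrictions for COVID-19 have been implemented", with no figure attached; this has no bearing on whether the arithmetic is right.
- *That 200 and 250 contradict each other.* Two separate indicative calculations may use different numbers. The difference is unexplained, not contradictory.

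**Conclusion.** The narrow point holds. The combination of 250 pairs, r = 0.2 (4% of variance) and 80% at p < 0.05, with r = 0.25 at p < 0.005, is not internally consistent. At 250 pairs and 80% power the detectable values are about 0.18 and 0.23; equivalently, power at the printed values is about 9 percentage points above the stated 80%. This rests on two-sided testing and the Fisher z approximation, and the alternative methods tried do not change it.

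The source of the error cannot be settled from the document. A reader might infer that the study is underpowered. It is not on this account: if 250 pairs are analysed, power is understated, and the printed correlations remain roughly right at 80% power down to about 200 pairs. This is a reporting error in a planning figure, with no consequence for the design.

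**What to change.** Restate the correlation figures as one consistent set. The sponsor should choose the set that matches the calculation actually made:

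- (a) 200 analysable pairs, about 80% power for r = 0.20 at p < 0.05 and r = 0.25 at p < 0.005 (81% and 78%). The loss assumption that links 250 recruited to 200 analysed should be added if the sponsor confirms there was one.
- (b) 250 pairs, 80% power for r = 0.18 (r² = 3.1%) at p < 0.05 and r = 0.23 at p < 0.005, noting that this assumes no loss.
- (c) 250 pairs, about 89% power for r = 0.2 at p < 0.05 and r = 0.25 at p < 0.005, on the same no-loss assumption.

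Whichever is chosen, repeat N and power beside the p < 0.005 figures and state that tests are two-sided, if they are. The cost is a sentence or two in the Sample size section; recruitment, sampling and analysis are unchanged.

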#### Cohort

Two hundred fifty healthy pregnant women will be recruited from across Norfolk. We will be recruiting participants from the maternity unit at a single major regional hospital, the Norwich and Norfolk University Hospital Foundation Trust (NNUH) which provides care for a population of approximately 1,000,000. The vast majority of women in the region will use the maternity services of this hospital. Participants will all be planning to give birth at NNUH or have a home birth with their maternity care provided by the NNUH. The total number of live births per year at NNUH is ~ 6000. Our primary objective is to describe the determinants, function and composition of maternal and neonatal microbiomes throughout pregnancy and early childhood in a cohort of mothers and their babies without serious health conditions. Therefore, we will be seeking a ‘healthy’ cohort of mothers, with the following inclusion and exclusion criteria applied.

